## Adverse Events

Any untoward medical occurrence in a patient, which does have a causal relationship with the treatment intervention, is considered an adverse event (AE).

Examples of AEs possible in this study include (but are not limited to): stress and/or anxiety induced by the study surveys; anxiety caused by contacting a deceased patient’s family.

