# Intervention and Implementation

The term ‘intervention’ refers to the Chronic Disease Management model applied to the care of the patient with cirrhosis of the liver. The intervention starts after randomisation and will continue until the end of the study which is 24 months after the first randomised patient.

Randomisation signals the start of the treatment period. Every Participant will have at 24 months of intervention.

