## Control/usual care group

Control/usual care patients will continue hospital and out of hospital management via usual care processes. To prevent contamination of usual care patients by the intervention, usual care patients will have no contact with CLD nurses until a final end of study interview. Usual care patients will be mailed surveys at baseline, 3 months, 6 months, and then 6-monthly until the end of the trial (24 months after the first patient randomised). At the end of the trial, control group participants are invited for a face-to-face review to complete the surveys, are given the Cirrhosis Booklet and offered an education session.

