## Data Monitoring

Outcome data for all endpoints will be monitored at 3-monthly intervals during the trial by the project team and at the trial midpoint to review adverse events, progress and preliminary outcome data.

Data will be submitted by scanning data collection records to the trial data manager. If a patient consents to receiving study surveys electronically, the CLD nurse involved in their care will send fillable surveys at each time point to the provided email address. The surveys will have the patient’s unique study ID allocated. Completed surveys will be emailed back to the CLD nurse, who will then check to ensure there is no identifying information recorded, before forwarding data on to the trial data manager as per standard process. All data will be saved in a secure password-protected computer for the duration of the study, which can only be accessed by the trial data manager.

| Activity Schedule for CONTROL patients | Baseline | Treatment Period  Day 7 to Week 11 are scheduled from the discharge date from hospital.  From Month 3 visits are scheduled from randomisation.  All visits/contacts have a window of +/- 2 days | | | | | | | | | | | | | | | | |
| --- | --- | --- | --- | --- | --- | --- | --- | --- | --- | --- | --- | --- | --- | --- | --- | --- | --- | --- |
|  | Baseline | Day 7 | Day 14 | Week  3 | Week  4 | Week  5 | Week  6 | Week  7 | Week  8 | Week  9 | Week  10 | Week  11 | Month  3 | Month  6 | Month  9 | Month  **12** | Month  18 | Month 24/EOS |
| Informed Consent | X |  |  |  |  |  |  |  |  |  |  |  |  |  |  |  |  |  |
| Child Pugh / MELD | X |  |  |  |  |  |  |  |  |  |  |  |  |  |  |  |  | X |
| SURVEYS (5) | X |  |  |  |  |  |  |  |  |  |  |  | X | X |  | X | X | X |
| Concomitant Medications | X |  |  |  |  |  |  |  |  |  |  |  |  |  |  |  |  | X |
| Comorbidities | X |  |  |  |  |  |  |  |  |  |  |  |  |  |  |  |  | X |
| Charlson Comorbidity Index | X |  |  |  |  |  |  |  |  |  |  |  |  |  |  |  |  |  |
| Randomisation | X |  |  |  |  |  |  |  |  |  |  |  |  |  |  |  |  |  |
| Cost/Resource use survey | X |  |  |  |  |  |  |  |  |  |  |  |  |  |  |  |  | X |
| Admissions to hospital |  |  |  |  |  |  |  |  |  |  |  |  |  |  |  | X |  | X |
| Liver-related appointments |  |  |  |  |  |  |  |  |  |  |  |  |  |  |  | X |  | X |
| Patient Satisfaction |  |  |  |  |  |  |  |  |  |  |  |  |  |  |  |  |  | X |
| Alcohol Use assessment |  |  |  |  |  |  |  |  |  |  |  |  |  |  |  |  |  | X |

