**…………………………………………………………………………………………………………………………………………………………………………**

## Appendix U – Diuretic Titration Guidelines for Trial Nurses

*This guideline has been developed to assist the ALFIE Nurses to provide timely diuretic titration to patients on these medications. As experienced RNs in the field of Gastroenterology and Hepatology, the ALFIE nurses have received training in diuretic titration during the Investigator Meetings in November 2017 and August 2018. Nurses are encouraged to check with a medical officer if in doubt.*

| Medicine Name: Frusemide (Furosemide) and Spironolactone (Adult) | |
| --- | --- |
| **Formulation:** | Frusemide (Furosemide): 20 mg tablet and 40 mg tablet  Spironolactone: 25mg tablet and 100mg tablet |
| **Specific Condition** | Non tense ascites secondary to advanced liver disease. |
| **Purpose and scope:** | Facilitate timely titration of diuretic treatment of non-tense ascites associated with liver failure, for adult patients enrolled in the ALFIE trial |
| **Limitations:** | Only applies to patients enrolled in the ALFIE trial |
| **Indications for use:** | Non-tense ascites associated with chronic liver disease:   - Patients must be able to monitor weight daily, either alone or with carer input. - Patients and/or carers must be able to understand and implement titration instructions. |
| **Contra-indications:** | - Patients with a known barrier to compliance. - Patients unable to be weighed daily. - Patients/carers unable to understand and implement titration instructions. - Patients with renal impairment who require a Medical Officers input regarding diuretic titration. - *Patients with stable chronic renal impairment may have their diuretics managed by the ALFIE nurse as per this guideline if instructed to do so by the patient’s attending Hepatologist.* - Patients with overt hepatic encephalopathy. |
| **Dose** | - This guideline covers patients who are currently prescribed frusemide (furosemide) and spironolactone by a medical officer for the management of non-tense ascites associated with chronic liver disease. - Doses of spironolactone and frusemide (furosemide) can be titrated up in increments of a half or full dose. - Usually both diuretics are titrated up together but at times dysfunction in electrolytes (Sodium or potassium) may necessitate titration of only one diuretic. - Doses must not exceed a maximum of frusemide (furosemide) 160mg daily or spironolactone 400mg daily. |

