| **Frequency:** | ALFIE trial nurses may instruct the patient to increase their dose of frusemide (furosemide) or spironolactone no more than every 5 days (following receipt of electrolyte test results). |
| **Procedure for administration:** | Patients/carers will monitor weight daily and those failing to show adequate weight loss over a five day period and with normal kidney function and electrolytes will be directed by the ALFIE trial nurse to increase their dose of diuretics. |
| **Management of Complications:** | Complications of diuretics:  **Renal failure:** refer to treating medical officer  **Hepatic encephalopathy:** refer to treating medical officer  **Electrolyte disturbances:**  **Hypokalaemia:** reduce if K+ <hold frusemide (furosemide) if serum potassium <3 mmol/L and recheck bloods within 72hrs.  **Hyperkalaemia:** reduce Spironolactone if serum potassium >5.6 mmol/L. Hold spironolactone if serum potassium >6.0 mmol/L. Recheck bloods within 72hrs  **Hyponatraemia:** Reduced diuretics if sodium <130mmol/L. Hold diuretics if sodium < 125 mmol/L. Recheck bloods within 72hrs  **Muscle cramps:** Check electrolytes. If severe, may require discontinuation; Discuss with Medical Officer.  Complications are to be managed by the ALFIE trial nurse and/or treating Medical Officer depending on the severity. |
| **Monitoring requirements:** | - Diuretic titrations up in dose should be followed by a blood test in 5 days and electrolyte imbalance managed with consideration of concomitant therapy (conducted by either the ALFIE trial nurse and/or treating Medical Officer). - Diuretic titrations down in response to kidney or electrolyte dysfunction should be monitored closely with blood tests. |
| **Documentation:** | Any dose changes are to be documented in the patient’s outpatient medical record/EPAS and the GP informed. |

| REFERENCES | |
| --- | --- |

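### The adverse event definition requires causation by the intervention, so harms managed without admission may go unrecorded and AE counts cannot be compared between arms

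*Protocol*

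**What the plan says.** The Adverse Events section of the protocol defines the term in one sentence: "Any untoward medical occurrence in a patient, which does have a causal relationship with the treatment intervention, is considered an adverse event (AE". It then gives an explicitly non-exhaustive list of examples: "stress and/or anxiety induced by the study surveys; anxiety caused by contacting a deceased patient" (the second concerns contact with the patient's family).

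Under Intervention and Implementation, the intervention "refers to the Chronic Disease Management model applied to the care of the patient with cirrhosis of the liver". The Control/usual care group section states that "usual care patients will have no contact with CLD nurses until a final end of study interview".

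Appendix U gives trial nurses a guideline for changing diuretic doses. Its stated purpose is: "Facilitate timely titration of diuretic treatment of non-tense ascites associated with liver failure, for adult patients enrolled in the ALFIE trial". Under the label "Complications of diuretics" it names renal failure, hepatic encephalopathy, low and high potassium, low sodium and muscle cramps.

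The Data Monitoring section plans a look at the data "at the trial midpoint to review adverse events, progress and preliminary outcome data".

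**The concern.** An AE record is useful for comparing arms when events are captured the same way in both, and relatedness is judged afterwards. Here the judgement comes first, and an event that fails it is not an AE. That has two consequences. The definition points at one arm only. Within that arm, the count depends on how readily someone attributes an event to the care model in a population where renal, electrolyte and neurological deterioration is also part of the disease.

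This matters because the intervention is not confined to education and telephone support. It includes nurse-directed diuretic titration, for which the protocol itself lists medical complications. The examples in the Adverse Events section mention none of them. A midpoint review working from this definition could see few or no such events, and could not tell whether they were absent or merely unattributed.

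**Working it through.** No arithmetic applies: the point is about a definition, and the protocol states no expected rate for these events. The check sets the sections against one another.

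**1. Can a control event qualify?**
- The definition requires a causal link to the intervention.
- The intervention is the chronic disease management model.
- Usual-care patients are kept away from the nurses who deliver it until the final interview.
- Read literally, then, no control event before that interview can be an AE.

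**2. Do the section's examples agree?** They do not.
- "stress and/or anxiety induced by the study surveys" arises from a study procedure, and usual-care patients are mailed those surveys too. On this example a control patient can have an AE.
- Anxiety in a deceased patient's family is not an occurrence in a patient at all.
- The definition and its examples therefore cannot both be applied as written.

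**3. Who decides on causality?**
- No section names an assessor.
- The section on randomization, stratification and blinding says care providers cannot be blinded but outcome assessors will be. It does not say which group judges AEs.

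**4. What is captured whatever the attribution?**
- Admissions: Appendix J records the primary reason, whether liver-related, whether a decompensation, emergency or elective, and intensive care days. Both activity schedules place this at month 12 and end of study.
- Deaths: recorded on the end-of-study form (Appendix Q) for both arms. The Mortality and disease severity section adds a registry cross-check for patients lost to follow-up.
- Child-Pugh and MELD: scheduled in both arms at baseline and end of study. The scheduled values at months 3, 6, 12 and 18 are for the intervention arm only.

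**5. What is left out?** Take a potassium disturbance after a dose change, handled as an outpatient.
- It creates no entry in the admission log.
- The Child-Pugh/MELD form (Appendix N) has fields for creatinine and sodium but none for potassium.
- The nurse contact log (Appendix M) records the type and date of contact, not the clinical content.
- Appendix U sends dose changes to the medical record and the GP, and complications to the trial nurse or the treating medical officer. It has no AE reporting step.
- Neither activity schedule nor the end-of-study checklist has an AE item in the text available.

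Such an event becomes an AE only if someone attributes it to the intervention, and only then does it enter the AE count for the midpoint review.

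**The case against.** The strongest reply is that serious harm is already well covered. Admissions with their reasons, intensive care days and deaths are collected in both arms without any causality filter, and all-cause and intensive care admissions are among the protocol's hospital-use measures. This stands. A reader might infer that no safety comparison between the arms is possible, or that no risk ratio could be estimated for any harm. The documents do not support that.

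A second reply is that the survey example, and the wording that the list is not exhaustive, show the authors meant something broader than the literal sentence. That is plausible, and it is why a flat statement that controls will have zero AEs goes too far. It does not repair the definition, because two sites could apply it differently and both be following the protocol.

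Third, a reader might infer that the nurses will judge the effects of their own titration. The text does not say so. Appendix U covers patients already prescribed these drugs by a medical officer, and it refers renal failure and encephalopathy to the treating medical officer. Attribution by unblinded staff is a reasonable inference, because care providers are unblinded and no assessor is named, but it remains an inference.

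Finally, the pilot's bed-day result might be read as a harm signal that this definition would hide. It should not be. The rate ratio was 1.6 with a 95% CI of 0.5 to 4.8, while unplanned admissions and mortality leaned the other way, also non-significantly. Bed days are measured in this trial however an AE is defined.

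**Conclusion.** The concern holds in a limited form. The definition makes AE capture depend on attribution and, read literally, confines it to one arm. It conflicts with its own examples and does not mention the complications listed in Appendix U. The midpoint AE review would rest on a selectively recorded count even if the protocol were followed exactly.

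The affected events are those that lead neither to admission nor to death. Their number cannot be estimated from the protocol. The primary outcome and the comparison of deaths and admissions are not affected. The definition should be amended, but it does not undermine the trial's main result.

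Two assumptions apply. Appendix U is taken to operate only in the intervention arm, since controls do not meet the nurses during follow-up. The absence of an AE form is judged only from the text available.

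**What to change.** - Define an AE as any untoward medical occurrence in a participant, whether or not it is considered related to the intervention. Apply this in both arms.
- Record relatedness as a separate field, and name who judges it.
- Reconcile the Adverse Events section with its own examples, with the complications in Appendix U, and with the midpoint review under Data Monitoring.
- Make deaths and admissions with reason, tabulated by arm, the main safety comparison at the midpoint and at the end. Both are already collected in both arms.
- List Appendix U complications found in existing records as supportive information, with the number of blood tests per arm. Appendix U asks for a blood test 5 days after each dose increase, and controls have no matching schedule. More testing finds more abnormalities, so an unadjusted laboratory comparison could show a spurious excess in the intervention arm.

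The cost is a wording amendment and modest record abstraction. The downside is more events to list in a sick population. No change to any dose or clinical rule is proposed.

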# Treatment of Participants

## Concomitant medications

Relevant information about all concomitant medications (Including prescribed, over-the-counter, or herbal preparations) taken from the start of the study to the end of the study must be recorded on the source document ‘concomitant medications’ (and submitted to for data entry at baseline and at the end of the trial.

## Randomisation

The study will be conducted in a randomised controlled manner. Allocation to one of two treatment groups (intervention or control) will occur on a 1:1 ratio across sites and will be stratified by aetiology. A randomisation list will be generated by a statistician and allocations, stratified by aetiology, will be placed into sealed opaques envelopes until randomisation. Upon consent, the CLD nurse will contact an independent researcher at FMC for telephone randomisation. Participant allocation, using unique study ID, will be recorded by the independent researcher and stored in a secure cabinet.

## Assignment of Site and Participant Numbers

Each study site will be assigned a site number by the coordinating site. The site number will be used to categorize Participant data and to identify the site and/or investigator within study documents. Participants will be identified using a unique 4 digit number. The first digit will represent the site number and the last three digit will represent the patient number. The patients are given sequential numbers (ie at each site the first patient will have number 001, then the second 002 etc).

# Visit Procedures

## Pre-Screening

Patients who are admitted with a liver-related issue will be assessed for eligibility for the study. Inclusion and Exclusion criteria are applied and patients who meet all criteria call be approached for consent. Patients with any diagnosis of Hepatic Encephalopathy need to have a documented West Haven Criteria Score of “0” before they are approached.

## Baseline

Baseline visits will begin after

- - The signature of the informed consent form (ICF)
  - The study number is allocated (Site Number-XXX)

### Baseline – all patients

Patients in the intervention and control group will have the following collected using the Baseline collection tool (Appendix A):

- - Demographics
  - Aetiology of cirrhosis
  - Child Pugh/MELD Score
  - All surveys (PIH, CLDQ, Cirrhosis Knowledge Assessment Questionnaire, EQ-5D-5L, ASK-12, and resource use survey)
  - Concomitant medication list (as per current hospital medication chart)
  - Comorbidities list and the Charlson Comorbidity index

Once all of the baseline information is collected Randomisation occurs via the telephone contact.

If a patient has been randomised to receive usual care, please advise them that they will be receiving future surveys by mail and that at the end of the trial they will be invited to come in for a face to face meeting and education. Ensure their address and contact details are correct.

### Baseline – intervention only

After randomisation, patients in the intervention group continue to have information collected which helps with the development of their care plan. It is best to collect this information as soon as possible after randomisation – but within 7 days of randomisation.

- GP communication informing of the patient’s involvement (see fax templates)
- Make appointment for home visit (if discharge date known) – complete safety check for home visit
- Ascites and HE assessment
- HCC assessment
- Osteoporosis assessment
- Alcohol assessment
- Variceal screening assessment
- Nutrition assessment
- Carer and GP assessment

The care plan can start to be developed at this point. Ensure that once the patient has discharged from hospital, they have an outpatient review by a gastroenterologist/Hepatologist scheduled within a month (4 weeks) of discharge. Please provide the patient with a participant identification card. Contact the GP by phone to establish accepted communication methods and communicate hospital discharge information.

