# Background

**Cirrhosis and chronic liver failure**

A variety of insults to the liver can lead to progressive fibrosis and cirrhosis. The most common causes in Australia include; alcohol abuse, chronic hepatitis C (HCV) infection, and non-alcoholic fatty liver disease (NAFLD). Ongoing injury to a cirrhotic liver may result in decompensation of liver functions or chronic liver failure (CLD). CLD is manifested by complications such as; ascites, variceal bleeding, encephalopathy, sepsis (most commonly spontaneous bacterial peritonitis) and renal dysfunction, protein calorie malnutrition and hepatocellular carcinoma (HCC). The prognosis following the onset of CLD is poor. Patients with early CLD (Child Pugh class B) have a 2-year survival of only 60% and this falls to 35% in advanced CLD (Child Pugh class C)([1](#_ENREF_1)).

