## Secondary Objectives

- To evaluate incremental cost effectiveness for this intervention, relative to usual care. Assessment of quality of life will be a necessary component of the economic analysis. The QALY will be used to assess this outcome.
- To evaluate the effect of CDM on mortality
- To evaluate the effect of CDM on the quality of care provided to patients in the intervention arm. This will be assessed using the following measures:
  - attendance at planned outpatient care;
  - medication adherence;
  - adherence to antibiotic prophylaxis protocols for patients with ascites;
  - adherence to variceal bleeding prevention protocols;
  - adherence and response to alcohol abuse treatment protocols in alcoholic liver disease patients; and
  - referral rates to liver transplantation assessment teams.
- To compare self-management ability and knowledge of patients in the CDM arm with usual care models.

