## Statistical methods

All analyses will be performed according to an intention-to-treat protocol. Differences between groups for hospitalization rates, quality indicators, satisfaction rates and self-management scores will be assessed using negative binomial regression, which is appropriate for count data with evidence of over-dispersion. All models will allow adjustment for baseline values and other co-variates. Suitable transformations will be applied in the case of non-normally distributed data.

For the economic analysis mean costs between the intervention and control groups will be compared and incremental cost effectiveness ratios presented with confidence intervals. Cost effectiveness acceptability curves for varying threshold values of cost effectiveness will also be presented ([46](#_ENREF_46)). An assessment of the sensitivity of the results obtained to variation in measured resource use, effectiveness and/or unit costs will be undertaken using appropriate one-way and multi-way sensitivity analysis ([47](#_ENREF_47)). Differences between groups in quality of life scores will be assessed using mixed effects regression to account for the repeated measures (every 3 months) and subsequent within-Participant correlation. Survival analysis will be performed using Cox regression with results presented as Kaplan-Meir survival curves.

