## Appendix E – Alcohol Assessment

**Timepoint ASSESSMENT COMPLETED:**  Baseline - Date: ____ / ____/ _____

End of Trial - Date: ____ / ____/ _____

| ***Alcohol use – prior to today’s assessment*** | | **Yes** | **No** |
| --- | --- | --- | --- |
| 1 | Has the patient drunk any alcohol in the last 6 months? (if yes, put on care plan) |  |  |
| 2 | If abstinent, date of last drink of alcohol (month and year) ______ / _______  month / year |  |  |
| 3 | If yes, specify alcohol amount:  Last 6 months:  Light (<2/day)  Moderate (2-4/day)  Heavy (>4/day)  Last 2 weeks:  Nil  Light (<2/day)  Moderate (2-4/day)  Heavy (>4/day) |  |  |
| 4 | Has patient seen Drug and Alcohol Services? (if no, arrange during inpatient stay) |  |  |
| 5 | Has an anticraving agent been prescribed? (If yes, add to medication list) |  |  |
| 6 | Is an anticraving agent being taken? (check with patient) |  |  |
| 7 | Has patient been referred to a psychologist for CBT/counselling? ( If no, add to plan of care for MHCP with GP and referral to psychologist) |  |  |

Comments:

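### Alcohol use at entry is recorded only in the intervention arm and only after randomisation, so the alcohol-treatment response measure has no control baseline

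*Protocol*

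**What the plan says.** The Secondary Objectives list, among six quality-of-care measures, "adherence and response to alcohol abuse treatment protocols in alcoholic liver disease patients". The Statistical methods section compares quality indicators between the groups and adds: "All models will allow adjustment for baseline values and other co-variates".

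The common baseline is set out under Baseline – all patients: demographics, aetiology, Child Pugh and MELD, the surveys, medications, comorbidities and the Charlson index. These come before allocation: "Once all of the baseline information is collected Randomisation occurs via the telephone contact". Neither that list nor the Appendix A tool has an item on drinking. Alcohol appears there only as a possible aetiology.

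The alcohol assessment comes under Baseline – intervention only, introduced by "After randomisation, patients in the intervention group continue to have information collected", with a limit of 7 days from randomisation. The activity schedules agree. The intervention schedule marks it at Baseline and at Month 24/EOS, the control schedule at Month 24/EOS only. The form itself (Appendix E) asks "Has the patient drunk any alcohol in the last 6 months" and then, for those who have, the amount over the last 6 months and the last 2 weeks.

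**The concern.** A measure of response to alcohol treatment is most naturally read against what the patient was drinking at entry. Here that starting point is recorded in one arm only. It is recorded after allocation, inside the treatment period, by a nurse who knows the allocation and delivers the intervention. Three things are lost for the between-arm comparison: change since entry, adjustment for entry drinking, and a check that the arms were alike in drinking at entry.

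The last of these matters to this trial in particular. The protocol criticises its own pilot for having more alcoholic liver disease in the usual care group. Stratifying by aetiology guards against that imbalance, but an alcohol aetiology does not say whether a patient is still drinking.

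**Working it through.** No sample size or power figure enters this point. The check is whether any planned record gives drinking at entry in controls.

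**Step 1: planned alcohol assessments** (Baseline sections, End of Study section, both activity schedules)

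| | Before randomisation | Within 7 days after | End of study |
|---|---|---|---|
| Control | 0 | 0 | 1 |
| Intervention | 0 | 1 | 1 |

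No patient in either arm has an assessment before randomisation. A model adjusted for baseline drinking would have no covariate values in the control arm.

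**Step 2: can the end-of-study form rebuild the control baseline?** The amount items reach back at most 6 months.
- At a month-24 visit they reach back to 24 − 6 = month 18 after randomisation.
- The End of Study section instead dates the visit 24 months after the first patient was randomised, and recruitment may run to 18 months. The last patient recruited could then be seen at 24 − 18 = 6 months. The look-back ends at 6 − 6 = month 0, so it covers only time since randomisation.
- Only a visit earlier than 6 months, such as an early withdrawal, would reach back past entry, and it would mix drinking before and after randomisation.

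The date of last drink is asked only of abstinent patients. A date before randomisation shows abstinence since before entry. A later date does not show whether the patient was drinking at entry, and neither gives an amount.

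**Step 3: can other baseline data substitute?** The medication list might show an anticraving drug and the comorbidity list might mention alcohol dependence. Neither records consumption. The protocol describes none of the baseline surveys as measuring it.

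**Step 4: is there another contact?** Under Control/usual care group, controls have no contact with the trial nurses until the final interview, so no later visit fills the gap.

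**Step 5: what survives?** The End of Study section schedules the form in both groups. Randomisation is stratified with alcohol as one of three strata, in blocks of four, so arm sizes within that stratum are close to equal. Drinking at end of study can therefore be compared between arms without a baseline.

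**The case against.** The strongest case on the other side is that the measure does not need a baseline. The protocol does not define response. Abstinence over the last 6 months, or amount over the last 2 weeks, read at end of study is a legitimate outcome, and randomisation protects the comparison. Adherence, the other half of the measure, can be read from items 4–7 at end of study. The adjustment sentence is permissive, and its paragraph also covers satisfaction, which is measured only at the end, so it cannot mean that every endpoint has a baseline. Aetiology, Child Pugh, MELD and Charlson are available before randomisation in both arms as covariates. All of this stands, and it keeps the point small. It does not supply the missing control value, and an analysis plan can define response but cannot create uncollected data.

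The objective speaks of care given in the intervention arm, which might suggest that no control data are needed. The analysis section, however, compares groups on these indicators. Appendix E prints a baseline tick-box without the intervention-only label used in Appendices C and R. The visit text and both schedules leave no doubt that controls are not assessed then.

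A reader might infer more, in three ways that the documents do not support:
- **That only completers have the form.** The activity table in Appendix Q is headed that way, but the End of Study section also schedules the visit at withdrawal and transplant listing, and Appendix Q itself asks for completion at listing. Deaths and losses to follow-up are the clear gaps.
- **That the background survival figures give the number left to analyse.** Those figures ("2-year survival of only 60" per cent in Child Pugh B, 35% in C) are not the trial's planning assumption, which is 20% attrition. Applying them to 75 per arm would also count all aetiologies, whereas the measure concerns alcoholic liver disease only, a stratum whose size is not given.
- **That baseline drinking would separate selective survival from effect.** Outcomes truncated by death stay truncated whatever is recorded at entry.

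The gain in precision from adjustment cannot be stated either. The items are categorical and the protocol gives no correlation between entry and end-of-study drinking.

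**Conclusion.** The point holds in a limited form. Entry drinking is missing in controls by design, and in the intervention arm it is recorded only after allocation. For one of six quality-of-care measures, change since entry and baseline adjustment are impossible in controls, and balance in drinking cannot be checked. The unadjusted end-of-study comparison within the alcohol stratum remains possible, and the primary outcome, unplanned liver-related admissions, is unaffected.

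The conclusion rests on the schedules being followed as written and on no baseline survey recording consumption. It justifies a cheap improvement to data collection. It does not show that the trial's conclusions would be biased.

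**What to change.** - Add Appendix E items 1–3 (any alcohol in 6 months, date of last drink, amount) to the pre-randomisation list under Baseline – all patients, to Appendix A, and to the Baseline column of the control schedule. Omit the care-plan prompt attached to item 1 from this common version.
- Keep items 4–7, which concern services and referrals and carry prompts to act, after randomisation in the intervention arm.
- State that end-of-study drinking will be compared between arms in alcoholic liver disease patients, adjusted for the baseline category.
- For patients already randomised, the value cannot be recovered. If the change is not made, say plainly that this measure is compared at end of study without baseline adjustment.

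The cost is a few minutes per patient at a visit that already takes place. It adds no contact with controls after allocation, so the rule against contamination is kept. Asking about drinking may itself change drinking slightly. Because it would do so in both arms it should not bias the comparison, but it could marginally dilute the contrast.
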